## Abstract

**Background:**

Primary dysmenorrhea (PD) is a leading cause of dysmenorrhea among adolescent girls. Manual acupuncture may be considered as an effective treatment for PD, but high-quality evidence remains limited. This trial aims to evaluate the efficacy and safety of acupuncture for the prevention of PD as compared with sham acupuncture and usual care.

**Methods/design:**

This is a three-arm, randomized, controlled clinical trial in which the patients, assessors, and statisticians will be blinded. A total of 300 acupuncture-naive patients who were diagnosed as PD will be randomly allocated to the verum acupuncture, sham acupuncture, or usual care groups in a 2:2:1 ratio. Patients in the verum acupuncture group will receive manual acupuncture at specific acupuncture points with penetrating needling, while those in the sham acupuncture group will receive non-penetrating needling at non-acupuncture points. They will be given five sessions over a menstrual cycle for 3 menstrual cycles. Patients in the usual care group will receive health education and informed to receive manual acupuncture for free after waiting for 7 menstrual cycles. The primary outcome will be the change from baseline in the Cox Menstrual Symptom Scale Score (CMSS). The secondary outcomes will be the changes in Massachusetts General Hospital Acupuncture Sensation Scale (MASS), visual analog scale (VAS), Short-Form McGill Pain Questionnaire 2 (SF-MPQ-2), Pittsburgh Sleep Quality Index (PSQI), Beck Anxiety Inventory (BAI), Beck Depression Inventory II (BDI- II), Acupuncture Expectancy Scale (AES), 60-item NEO Personality Inventory-Short Form (NEO-FFI), and acute medication intake. The adverse events will be recorded at every visit. The analyses will be performed base on a full analysis set (FAS) and a per-protocol set (PPS).

**Discussion:**

This study may provide high-quality evidence regarding the efficacy and safety of manual acupuncture for PD. In addition, the results of this study will help to identify the efficacy of acupuncture due to the specific effects of acupuncture or placebo effects of acupuncture ritual.

**Trial registration:**

Clinical Trials.gov NCT02783534. Registered on 26 May 2016

## Background and rationale

Primary dysmenorrhea (PD), defined as painful menstruation in the absence of pelvic pathology, characteristically begins when adolescents attain ovulatory cycles, usually within 6–12 months of menarche [1]. It is estimated to affect 93% of adolescents in Australia [2], 68.1–72.2% in Turkey [3], 56.15% in India [4], 51.1% in China [5], and 46.8% in Japan [6], with a very severe pain accounting for 5.4 to 17.7% [5, 6]. The burden of PD is large; it is one of the leading causes of quality-adjusted life year loss in women [7]. In addition, women with PD had significantly higher scores of depression and anxiety than those without PD [8]. The current medical treatment for PD is symptomatic, often with nonsteroidal anti-inflammatory drugs and combined oral contraceptives pills [9]. However, the failure rate may reach up to 20–25% [9]. Hence, an effective and safe therapy for PD prophylaxis is still required.

Acupuncture is an important component of traditional Chinese medicine and may offer a non-pharmacological approach for PD prophylaxis. Many clinical trials have demonstrated the efficacy of acupuncture in the relief of PD. Such studies have been summarized in several recent reviews [10, 11]. However, the available evidence of the efficacy of acupuncture for PD remains insufficient because many clinical trials have had small sample, short follow-up, risk of bias, or other methodological limitations.

In clinical practice, two acupuncture manipulations were widely used: manual acupuncture and electrical acupuncture. Manual acupuncture is used as an analgesic therapy for more than 2000 years and is usually practiced by traditional acupuncturists. It is defined as the insertion of fine needles into specific acupoints and followed by the manual manipulation (i.e., intermittent rotation as well as lift and thrust) of needles [12]. The analgesic effects of manual acupuncture manifest when the stimulation reached a threshold allowing to generate *de qi* sensations [12]. In animal experiments, acupuncture needle rotation can trigger an increased release of adenosine and endogenous opioids and in turn regulate the analgesic effects of manual acupuncture [13, 14]. Therefore, the current trial is designed to evaluate the effect of manual acupuncture for the prevention of PD.

### Objectives

Through this study, we expect to test the following hypotheses: (1) evaluate whether manual acupuncture is superior to sham acupuncture and usual care for the prevention of PD and (2) identify whether the efficacy of acupuncture is due to the specific effects of acupuncture or placebo effects of acupuncture ritual.

### Trial design

This will be a multicenter, stratified, three-arm, randomized, controlled trial. A total of 300 eligible patients will be randomized in a 2:2:1 ratio to receive verum acupuncture, sham acupuncture, or usual care. This trial has been registered on the ClinicalTrials.gov protocol registration system (NCT02765581). The study design is presented in the flowchart in Fig. 1. The Standard Protocol Items: Recommendations for Interventional Trials (SPIRIT) checklist is provided as Additional file 1.

**Fig. 1 Fig1:**
[figure not shown]
Flowchart of the trial procedures

### Inclusion criteria

The following are the inclusion criteria:
Being diagnosed with PD according to the Primary Dysmenorrhea Consensus Guideline established by the Canadian Institute of Obstetrics and Gynecology in 2005 [15]Aged between 15 and 40 without a history of deliveryHave a history of regular menstrual cycles (28 days ± 7 days)Experiencing an average menstrual pain visual analog scale (VAS) score between 40 and 80 for at least 6 monthsAcupuncture naiveAble to complete the baseline PD diaryAble to sign an informed consent

### Exclusion criteria

The following are the exclusion criteria:
Secondary dysmenorrhea caused by endometriosis, pelvic inflammation, uterine myomas, or other gynecological problems confirmed by type B ultrasound exam by gynecologistsHaving a history of pelvic or abdominal surgeryCombined with uncontrolled diagnosed psychiatric disorders such as severe anxiety and depression, or severe systemic diseases affecting the implementation of treatment programsReceived any other treatment for PD 3 months prior to enrollmentPregnant women, women in lactation, and those planning to become pregnantExperience of acupunctureIlliterate or patients unable to read and understand questionnaires

### Consent to participate

This study will be conducted in accordance with the Declaration of Helsinki [16]. After being informed of the potential benefits and risks, all subjects will be required to provide informed consent prior to enrollment in the trial. In each sub-center, two independent gynecologists are responsible for recruiting the patient and gaining informed consent. On the consent form, participants will be asked if they agree to the use of their data if they choose to withdraw from the trial. Participants will also be asked for permission for the research team to share relevant data with people from the universities taking part in the research or from regulatory authorities, where relevant. This trial does not involve collecting biological specimens for storage. No changes are made to the trial protocol after the subject recruitment started.

### Interventions

To improve patients’ adherence to interventions, acupuncture will be performed by acupuncturists with over 5 years of clinical acupuncture experience and obtained a license from the Ministry of Health of the People’s Republic of China. Before performing the treatment, acupuncturists will receive centralized training. The training courses include an introduction to the basic clinical research methods and a practical demonstration of the treatment. Patients will be treated once a day for 5 consecutive days (a treatment course), start from the 5th or 7th day before the estimated first day of the latest menstrual cycle. A total of 3 consecutive treatment courses will be administrated. Each treatment session will be 30 min in duration. Streitberger acupuncture needles and Streitberger placebo needles will be used for the treatment, which is proven to be a validated and reliable single-blind acupuncture needle used to investigate the effects of acupuncture [17].

### Manual acupuncture

For the verum acupuncture group, manual acupuncture treatment will be applied to both obligatory and additional points using Streitberger acupuncture needles. The obligatory points include RN4 and bilateral SP 6, EX-CA1, and SP10. Additional points will be chosen according to different syndromes: bilateral ST36 for the deficient syndrome and bilateral SP8 for the sufficiency syndrome. Table 1 describes the acupuncture point prescription. After sterilizing the skin, sterile and disposable Streitberger acupuncture needles (0.30 mm in diameter and 30 mm in length) will be inserted into the acupuncture points. *De qi* sensations will be obtained through the manipulation of needles (rotating the needles 80–120 times per minute). During the 30-min acupuncture session, the manipulation of needles for each acupuncture point will last 10 s and will be repeated 4 times to induce lasting *de qi* sensations.

**Table 1 Tab1:** Details of the acupoints used in the verum acupuncture group

Acupoints (standard abbreviation/Chinese nomenclature)	Location	Indication	Insertion depth (cun*)
RN4/Guanyuan	On the anterior midline, 3 cun^a^ below the umbilicus	Coordinates Chong and conception vessels	1 to 1.5
SP6/Sanyinjiao	3 cun directly above the tip of the medial malleolus	Nourishes kidney and liver yin	1 to 1.5
EX-CA1/Zigong	4 cun below the umbilicus and 3 cun lateral to the anterior midline	Regulates the menstrual cycle and relief menstrual pain	0.8 to 1.2
SP10/Xuehai	2 cun above the upper border of the medial patella when the knee is fixed	Activates blood circulation to dissipate blood stasis	1 to 1.5
ST36/Zusanli	One-finger width lateral to the anterior border of the tibia and 3 cun directly below the lateral depression of the patellar ligament	Nourishes the spleen and stomach and coordinates qi and blood	1 to 2
SP8/Diji	On the line joining the tip of the medial malleolus and posteroinferior to the medial condyle of the tibia and 3 cun below the medial condyle of the tibia	Nourishes the spleen and disinhibit uninhibited dampness	1 to 2

*A cun is a measurement used to locate acupoints and corresponds to the distance between the two medial ends of the creases of the interphalangeal joints when the patient’s middle finger is flexed

### Sham acupuncture

For the sham acupuncture group, Streitberger placebo needles will be applied at 510 non-acupuncture points, located bilaterally on the back, at a distance of 5 cun lateral to the sixth, seventh, eighth, ninth, and tenth thoracic spine, respectively. No meridians pass through the location of these non-acupuncture points. Because the Streitberger placebo needle is non-penetrating, the acupuncturist will fix a small plastic ring over the point, and then stick the needle through the plaster inside the ring. This will fix the needles on the surface of these non-acupuncture points. Other acupuncture rituals will be identical to the verum acupuncture group.

### Usual care

For the usual care group, patients will be provided with 15 sessions of manual acupuncture treatment for free after a waiting period of 7 menstrual cycles. All of the three groups will receive health education. Health education will include the following aspects: (1) patients will be encouraged to engage in an appropriate exercise training program, (2) patients will be instructed to avoid raw and cold food, and (3) patients will be given relaxing training and psychological counseling.

### Co-interventions

In order to avoid confounding factors in the results of the trial, patients will be asked to avoid commencing other co-interventions for PD during the whole period of this study. In case of severe pain, diclofenac sodium enteric-coated tablets (25 mg/tablet; maximal tolerated dose = 200 mg/day) will be allowed as a rescue medication. Patients will be instructed not to take any other analgesics.

### Criteria for discontinuing interventions

Acupuncture will be ended if participants meet any of the following conditions:
Had serious adverse events during or after treatmentMisdiagnosed after randomizationPatients found to be pregnant after randomization

### Provisions for post-trial care

There is no anticipated harm and compensation for trial participation.

### Outcome measures

#### Primary outcome measure

##### Cox Menstrual Symptom Scale

In this study, the primary outcome will be the changes in Cox Menstrual Symptom Scale (CMSS) scores from baseline to menstrual cycle 6 after randomization based on the dysmenorrhea diaries. The changes in CMSS from baseline to other menstrual cycles (menstrual cycles 1–5 after randomization) will also be assessed. CMSS has been widely used for integrally evaluating patients’ dysmenorrhea symptoms [18]. In the severity evaluation, each symptom is scored via five levels, 0 denotes that the symptom is not noticeable, while 4 denotes it as very severely bothersome. In the duration evaluation, each symptom is scored in five grades, 0 denotes that the symptom did not occur, while 4 denotes that it lasted several days.

#### Secondary efficacy outcome measures

##### Massachusetts General Hospital Acupuncture Sensation Scale

Massachusetts General Hospital Acupuncture Sensation Scale (MASS) has been proposed as a useful tool for measuring *de qi* sensations in acupuncture research [19]. It includes 12 descriptors (soreness, aching, deep pressure, heaviness, fullness/distension, tingling, numbness, sharp pain, dull pain, warmth, cold, and throbbing) that are associated with the acupuncture treatment and one additional field allowing patients to describe the acupuncture sensation in their own words. Prior to the first treatment, the acupuncturist will give participants a brief description of *de qi* sensations. Participants will be asked to rate the intensity of experienced *de qi* sensations immediately after each acupuncture session. Patients in the usual care arm will not receive this questionnaire.

##### Visual analog scale

VAS is a simple and frequently used method for the assessment of variations in the intensity of pain [20]. We will use a 10-mm (0 = no pain, 10 = worst pain ever) VAS to assess the efficacy of acupuncture for pain relief. VAS score of each menstrual pain day will be recorded in a dysmenorrhea diary. The VAS will be assessed at baseline and during the first, second, third, fourth, fifth, and sixth menstrual cycles after randomization.

##### Short-Form McGill Pain Questionnaire 2

Short-Form McGill Pain Questionnaire 2 (SF-MPQ-2) is a highly reliable instrument to evaluate neuropathic and non-neuropathic pain conditions [21]. It is used as a complementary index of pain relief. The SF-MPQ-2 will be assessed at baseline and during the first, second, third, fourth, fifth, and sixth menstrual cycles after randomization.

##### Pittsburgh Sleep Quality Index

Pittsburgh Sleep Quality Index (PSQI) is a self-rated questionnaire which assesses sleep quality and disturbances over a 1-month time interval [22]. It has 19 questions which can be grouped into seven categories: subjective sleep quality, sleep latency, sleep duration, habitual sleep efficiency, sleep disturbances, use of sleeping medication, and daytime dysfunction. The PSQI will be assessed at baseline and during the first, second, third, fourth, fifth, and sixth menstrual cycles after randomization.

##### Intake of acute medication

The intake of diclofenac sodium enteric-coated tablets will be recorded in the dysmenorrhea diary and will be calculated during each menstrual cycle.

#### Secondary psychological outcome measures

##### Beck Anxiety Inventory

The 21-item Beck Anxiety Inventory (BAI) self-report questionnaire is a reliable and valid measure of anxiety severity [23]. In this study, BAI will be measured at baseline, menstrual cycle 3, and menstrual cycle 6 after randomization.

##### Beck Depression Inventory II

BDI has good sensitivity and specificity for major depression in chronic pain patients [24]. It contains 21-item, cutoff scores of > 20 (high) and < 14 (low) were adopted for depression symptoms. Beck Depression Inventory II (BDI-II) will be measured at baseline, menstrual cycle 3, and menstrual cycle 6 after randomization.

##### NEO Personality Inventory-Short Form

The 60-item NEO Personality Inventory-Short Form (NEO-FFI) is a self-administered personality test, scored on the five domains of neuroticism, extraversion, openness, agreeableness, and conscientiousness [25]. It has been widely used for pain patients and demonstrates good psychometric properties [26]. NEO-FFI was only measured once at baseline.

##### Acupuncture Expectancy Scale

Acupuncture Expectancy Scale (AES) is a simple four-item instrument with a valid and reliable score that measures expectancy about acupuncture therapy and correlates to subject reported response [27]. Patients in the verum acupuncture and sham acupuncture groups will be assessed using AES before the first acupuncture session and after completing the third and fifth acupuncture sessions. Patients in the usual care arm will not receive this questionnaire because they only receive compensatory acupuncture treatment after completing the whole study.

### Adverse events

The frequency of adverse events (AEs) will be recorded during the treatment period. AEs will not be recorded in the usual care arm.

### Assessment of blinding

After patients completed the whole visit, they will be asked to guess which type of acupuncture they received.

### Participant timeline

The participant timeline is described in Table 2.

**Table 2 Tab2:** Participant timeline

Period	Baseline		Treatment			Follow-up		
Menstrual cycle	− 1	0	1	2	3	4	5	6
**Participants**								
Screening	√							
Demography	√							
Informed consent	√							
PD diary	√		√	√	√	√	√	√
Randomization		√						
**Interventions**								
Verum acupuncture			√	√	√			
Sham acupuncture			√	√	√			
Usual care			√	√	√			
**Outcomes**								
CMSS	√		√	√	√	√	√	√
VAS	√		√	√	√	√	√	√
SF-MPQ-2	√		√	√	√	√	√	√
PSQI	√		√	√	√	√	√	√
BAI	√				√			√
BDI- II	√				√			√
NEO-FFI	√							
AES			√		√			
MASS			√	√	√			
**Trial safety evaluation**								
Adverse events			√	√	√			
Assessment of blinding								√

*AES* Acupuncture Expectancy Scale, *BAI* Beck Anxiety Inventory, *BDI-II* Beck Depression Inventory II, *CMSS* Cox Menstrual Symptom Scale, *MASS* Massachusetts General Hospital Acupuncture Sensation Scale, *NEO-FFI* NEO Personality Inventory-Short Form, *PD* primary dysmenorrhea, *PSQI* Pittsburgh Sleep Quality Index, *SF-MPQ-2* Short-Form McGill Pain Questionnaire 2, *VAS* visual analog scale

### Sample size

The sample size was estimated using the Statistical Analysis System software program (version 9.3; SAS Institute Inc., Cary, NC, USA). According to our pilot trial, we anticipate a greater CMSS score decline of 0.2 ± 0.55 in the verum acupuncture group compared with the sham acupuncture group. This sample size calculation is based on a superiority design with a power level of 80% and a significance level set at 5%, with a 1:1 ratio. Based on these assumptions, 170 patients will be needed, with 85 patients in each group. Moreover, we anticipate a greater CMSS score decline of 0.5 ± 1.15 in the verum acupuncture group compared with the usual care group. This sample size calculation is based on a superiority design with a power level of 80% and a significance level set at 5%, with a 2:1 ratio. Based on these assumptions, 150 patients will be required, including 100 patients in the verum acupuncture group and 50 patients in the usual care group. This sample size will be inflated to 300 to account for an attrition rate of 20%. Thus, we plan to enroll 300 patients, including 120 patients in the VA and SA groups and 60 patients in the usual care group.

### Recruitment

Eligible patients will be recruited through three strategies. First, patients will be recruited from the outpatient and inpatient clinics of the five hospitals. Second, patients will be recruited through Public Accounts of hospitals. Third, patients will be recruited from nearby communities and schools through the printed recruitment posters.

### Allocation

After completing a baseline evaluation, eligible participants will be randomly allocated to the verum acupuncture group, the sham acupuncture group, or the usual care group in a 2:2:1 ratio by an independent investigator. The 2:2:1 ratio was used to facilitate recruitment and increase the compliance of patients. The randomization sequences will be generated in a centralized manner via an interactive web response system with stratified centers and block size of 5. The independent investigator will provide the random sequence and group assignment immediately to the project acupuncturist within opaque, sealed envelopes. To prevent selection bias, the acupuncturists will be the only persons to know the patient’s group assignment prior to treatment. Central randomization has strict limits regarding authority; no one can check the files except the top principal investigator.

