### Blinding

In this study, many efforts will be done to maintain blinding in participants assigned to the verum acupuncture and sham acupuncture groups. For example, eligible patients will be acupuncture naive, we will set up the standardized ritual operations in the two groups as far as possible. However, patients in the usual care group will not be blinded. They will be provided with 15 sessions of manual acupuncture treatment for free after a waiting period of 7 menstrual cycles. This will increase the compliance of patients allocated to the usual care group. In addition, the acupuncturists will not be blinded.

We will try to ensure that the outcome assessors and statisticians are unaware of the group allocation by (1) using A, B, and C to label the three groups, (2) will randomly assign outcome assessors to follow-up, (3) allocation sequence will be concealed until the end of the study. In addition, we will separately give relevant data of MASS, AEs, and AES to an independent statistician for analysis, while the statistician responsible for the analysis of primary outcome and other secondary outcomes will be blinded to group allocation.

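### A single block size of 5 within centre, beside an open arm and unblinded acupuncturists, leaves a sizeable share of allocations predictable to an informed observer

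*Protocol article*

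**What the plan says.** All references are to the protocol article.

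- **Ratio and blocks (Allocation).** Patients are allocated to verum, sham or the "usual care group in a 2:2:1 ratio by an independent investigator". Sequences are generated centrally by a web response system "with stratified centers and block size of 5". No other block size is named, and nothing says that the size varies or is kept from the sites.
- **Centres (Recruitment).** Patients come from the "outpatient and inpatient clinics of the five hospitals", among other routes.
- **Who is unblinded (Blinding).** The text says that "patients in the usual care group will not be blinded", and then: "In addition, the acupuncturists will not be blinded".
- **What reaches the acupuncturist (Allocation).** "The independent investigator will provide the random sequence and group assignment immediately to the project acupuncturist within opaque, sealed envelopes". Before treatment the "acupuncturists will be the only persons to know" the assignment.
- **Concealment (Blinding).** Among the measures meant to keep assessors and statisticians unaware of allocation is that the "allocation sequence will be concealed until the end of the study".
- **Safeguards.** Two independent gynecologists per sub-centre recruit and take consent (Consent to participate). Only the top principal investigator may open the randomization files (Allocation). Screening, consent and the baseline diary precede randomization by a cycle (Table 2). Acupuncturists learn the assignment only shortly before treating (Discussion).

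**The concern.** A block of five at 2:2:1 contains exactly one usual-care slot. Because usual care involves no needling and is not blinded, a past usual-care assignment can be recognised by anyone who learns what happened to that patient. Once it has occurred in a block, the rest of that block is known to be needled. If four needled patients have passed, the fifth is known to be usual care. An acupuncturist, who sees verum and sham apart, can deduce more.

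At stake is selection at enrolment. If a forecast of the next allocation reached those who decide when a patient enters, keener or more severely affected patients could be steered towards needling. The baseline diary is complete before randomization, so severity is known by then. The comparison most exposed is verum versus usual care, which has its own sample-size calculation and rests on a patient-completed diary score. The Allocation section presents its procedure as preventing selection bias, and the Discussion calls the concealment adequate. The stated scheme supports those claims less well than it could.

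**Working it through.** The protocol gives no predictability figure to reproduce.

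**Inputs.** Ratio 2:2:1 and block size 5 within centre (Allocation); 300 patients as 120, 120 and 60 (Sample size); five hospitals (Recruitment). Consistency: 300/5 = 60 blocks, and 60 × (2, 2, 1) = (120, 120, 60), so the planned split fits complete blocks of five. The number of orderings per block is 5!/(2! × 2! × 1!) = 30, all equally likely.

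**Observer A: knows the block size, where blocks start, and earlier usual-care assignments only.** The question is whether the next patient is needled or usual care. At position k the usual-care slot has already been used with probability (k − 1)/5. At position 5 the remaining 1/5 is also certain, because four needled patients leave only usual care.

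**Observer B: knows every earlier allocation in the centre.** The exact arm is certain when all remaining slots belong to one arm. At position 4 this needs the last two slots to be both verum or both sham: 2 of the C(5,2) = 10 possible pairs, or 20%. At position 5 it is always so. The best guess picks the arm with most slots left:
- Position 1: 2/5.
- Position 2: 2/4 in every case.
- Position 3: 2/3 with probability 0.6 and 1/3 with probability 0.4, so 0.533.
- Position 4: 0.2 × 1 + 0.8 × 1/2 = 0.60.
- Position 5: 1.

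| Position | 1 | 2 | 3 | 4 | 5 | Sum | Share of 5 |
|---|---|---|---|---|---|---|---|
| A: needled or usual care certain | 0 | 0.20 | 0.40 | 0.60 | 1.00 | 2.20 | 44% |
| B: exact arm certain | 0 | 0 | 0 | 0.20 | 1.00 | 1.20 | 24% |
| B: best guess correct | 0.40 | 0.50 | 0.533 | 0.60 | 1.00 | 3.033 | 60.7% |

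Over 300 patients, 44% is 132 allocations and 24% is 72. With no information the best guess of the exact arm is right 40% of the time.

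Observer A's 2.20 divides into 0 + 0.2 + 0.4 + 0.6 + 0.8 = 2.0 allocations certain to be needled and 0.2 certain to be usual care. So the exact arm is certain for 0.2/5 = 4%. Most of the 44% is therefore certainty that the next patient will not be usual care, in a trial where 80% are needled anyway.

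**Alternatives, Observer B.** Fixed blocks of 10 and 15 come from exact recursion over the remaining slots. The random mixes come from simulating 60 patients per centre (300/5, assuming equal centres) with a guesser who knows the set of sizes but not the current one.

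| Scheme | Exact arm certain | Best guess correct |
|---|---|---|
| Fixed 5 | 24.0% | 60.7% |
| Fixed 10 | 13.7% | 55.9% |
| Fixed 15 | 9.5% | 53.4% |
| Random 5 or 10 | about 6% | about 57% |
| Random 5, 10 or 15 | about 3% | about 55% |

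For Observer A the certain share falls from 44% at a fixed 5 to 28.9% at a fixed 10 and 21.5% at a fixed 15. It was not computed for the random mixes.

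**The case against.** The strongest reply is that those who could predict are not those who enrol. Recruitment and consent belong to independent gynecologists, an independent investigator allocates after the baseline evaluation, and acupuncturists have no stated part in recruitment. The 24% and 61% describe what an acupuncturist might work out, so bias on that route needs information to leak. Timing helps too: a patient consents and completes a diary cycle before a slot is drawn, and others at the centre may be randomized meanwhile, so steering would need a forecast of block position or a delay after consent. All of this stands and lowers the risk. It does not remove it, since none of these measures hides past usual-care assignments, and closed files do not stop deduction from a known block size.

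Three stronger readings are tempting but not supported:

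- **That the whole sequence goes to the acupuncturist, making every allocation predictable.** The sentence allows that reading. But delivery is immediate and in sealed envelopes, file access is restricted, and the Blinding section promises to conceal the sequence. The phrase can equally mean one patient's random number and arm. It is a wording conflict, not established disclosure.
- **That everyone at a site sees who is in usual care.** The protocol says only that these patients are unblinded, and it describes efforts to keep assessors unaware.
- **That sites knew the block size, or that it was public during recruitment.** The article states the size and reports ongoing enrolment, but shows no publication date and does not say what sites were told. That the size never varied is itself inferred from a single value being given.

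It is also fair that varying the blocks removes most of the certainty but only part of the guessing advantage (61% to about 55%).

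**Conclusion.** The point holds as a weakness in the stated randomization scheme. It is not evidence that selection occurred. At most, 44% of allocations are certain as needled versus usual care to someone who sees only the open arm. At most, 24% are certain as to exact arm, with 61% guessed correctly against 40% by chance, for someone who sees all arms. These bounds assume a constant block of five and an observer who knows the size, the block boundaries, the enrolment order and the relevant earlier allocations. Real exposure is lower by an amount the protocol does not allow one to calculate, and no effect on the CMSS result is estimated. The exposure concerns mainly verum versus usual care: the open arm alone says little about verum versus sham. The handling of the random sequence is a separate wording matter to reconcile. Together these merit an inexpensive improvement.

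**What to change.** 1. For remaining enrolment, use randomly varying block sizes within centre (for example 5, 10 and 15) and withhold the sizes from site staff until recruitment closes. For an observer of all arms this takes certain allocations from 24% to about 3% and correct guesses from 61% to about 55%.
2. Reconcile the Allocation sentence on what the acupuncturist receives with the concealment statement under Blinding. State that only the current patient's assignment is released, after eligibility and baseline data are locked.
3. In the trial report, give the block size or sizes used, who could see earlier allocations at each centre, and baseline balance by centre.

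The cost is a reconfiguration of the web system and a few lines of protocol text. The downside is slightly larger possible imbalance within a centre. Recruitment began in August 2016 and was expected to end in July 2021, so step 1 protects only patients not yet randomized. If recruitment has closed, steps 2 and 3 still apply, with step 2 as a clarification of what was actually done.
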